## Methods

### Study design

This study will pilot test a social network-based group intervention that aims to empower and mobilize women who have been screened for CC to advocate for CC screening and treatment in female members of their social network (referred to as “alters”). We will pilot the intervention in a randomized controlled trial of 40 women who have been screened for CC (referred to as index participants), with 20 randomly assigned to receive the intervention (in two groups of 10) and 20 to the wait-list control [(each evenly stratified by age (under and over age 35) and history of CC-related treatment)]. Individual randomization entails risks for contamination, but statistical models suggest that ≥ 30% of the control arm must receive the equivalent of a full-strength intervention to result in meaningful contamination [24]. We opted for the wait-list control rather than an attention control, because this provides clearer findings for policy makers when considering intervention effects, and adequate control for attention may not be feasible given the 2-h duration and group dynamics of the workshops. The control arm receives the intervention after the completion of month-6 follow-up assessments. There is no way to blind the participants on whether or not they receive the intervention; this could potentially influence the outcomes, as clients may feel more or less incentivized to perform well in light of whether or not they receive the intervention. We do not see a way to prevent this potential bias, nor a way to distinguish such effects from actual intervention effects, but this limitation will be cited in reports of study findings. Data will be collected at baseline and month 6 from index participants and up to three alters of each index participant (max. total = 120 alters) who have not previously screened for CC. The primary outcome is alter CC screening over the 6-month follow-up period; secondary outcomes are index participant reported engagement in CC screening advocacy, internalized CC stigma, and disclosure of CC screening experience.

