The adapted intervention consists of 7 workshops. *Workshop 1* focuses on *addressing fears and concerns related to CC risk and use of self-compassion and peer support to overcome these fears*, as well as introducing the overall vision for empowering women to become change agents for CC prevention and treatment. With participants feeling more supported, *Workshop 2* focuses on *building skills and decision-making for sharing one’s personal CC screening experience*, knowing to whom to disclose and when and how to initiate and navigate disclosure and conversations about CC. *Workshop 3* builds skills and motivation for *healthy living* so that their own behavior (e.g., good nutrition, periodic VIA screens) is consistent with the behavior they encourage in others, as well as learning facts and myths related to CC to facilitate accurate CC screening advocacy. *Workshop 4* introduces the concept of a social network and how one’s network can serve as a tool for CC prevention advocacy and dissemination of CC-related information. *Workshops 5 and 6* focus on the skills needed for successful *CC-related advocacy*, including strategies for how to start conversations about CC and to keep these discussions going, as well as learning effective communication skills (e.g., reflective listening, paraphrasing, open-ended questions). *Workshop 7* inspires a *commitment to ongoing CC advocacy* through peer solidarity and support. The workshops will be conducted using a structured facilitator manual, in the predominant local languages of Samia and Lusoga, by two trained women from Namayingo who have experience being screened for CC. Using principles of compassion-focused therapy [27], the workshops will be administered in a group format to facilitate the use of *sharing of experiences* to build support, solidarity, and motivation among participants; *group problem-solving* and *role playing* to build skills and self-efficacy; *setting personal goals* regarding healthy living, disclosure, and advocacy; and homework to reinforce practice of new skills and generate personal experiences to be processed in the workshops. The seven workshops will be conducted weekly over 2 months, and each workshop will last 2 h. Participants will receive 30,000 Uganda shillings (~US $8) for attending each workshop to cover transport costs.

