### Statistical analysis

To assess feasibility and acceptability, we will examine recruitment (percent of screened women and social network members who are approached to participate, decide to enroll), retention, workshop attendance, and participant feedback elicited in the process measures. To assess intervention effects on alter CC screening, *w*e will use an intent-to-treat approach. In addition to comparing the arms at each time interval (baseline, month 6), we will apply logistic generalized mixed models to our repeated-measure data to examine intervention effects, using an indicator for study arm, and time by arm interaction to indicate whether change differs between the arms. We will use imputation for item nonresponse and attrition weights to account for nonrandom dropouts using logistic regressions; if dropout is random, analyses will incorporate design effects. We will explore the sensitivity of significance levels and conclusions to a range of plausible ICC values (.005 to .05) for the outcomes. We will control for and examine interaction effects with intervention process variables (e.g., number of workshops completed) and characteristics of the index participant (e.g., age), as well as the alter (e.g., position in the network, knowledge of index participant’s CC risk).

We will explore factors that may mediate the intervention effects on the primary outcomes among variables targeted by the intervention*,* such as internalized CC stigma, disclosure (percentage of alters disclosed to), and engagement in CC screening advocacy. The sample size may be too small to do mediation analysis, but we will examine how potential mediators are associated with the primary outcomes and treatment condition using bivariate statistics.

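### Controlling for workshops completed, which is post-randomisation and zero in every control, conflicts with intent-to-treat wherever it enters the model as a predictor of month-6 screening

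*Protocol article*

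**What the plan says.** All references are to the protocol article.

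- **Statistical analysis.** For intervention effects on alter screening, the primary outcome, the investigators "will use an intent-to-treat approach". They will compare the arms at baseline and month 6, and fit logistic mixed models to the repeated measures "using an indicator for study arm, and time by arm interaction to indicate whether change differs between the arms". Later in the same paragraph: "We will control for and examine interaction effects with intervention process variables (e.g., number of workshops completed". That sentence goes on to list index and alter characteristics. It is not labelled secondary or exploratory, and it is not limited to the intervention arm.
- **Study design.** "The control arm receives the intervention after the completion of month-6 follow-up assessments". Randomisation is "evenly stratified by age (under and over age 35) and history of CC-related treatment".
- **Intervention.** "The adapted intervention consists of 7 workshops", and "The seven workshops will be conducted weekly over 2 months, and each workshop will last 2 h".
- **Participants.** Index women are randomised after consent and the baseline assessment. Alters must report never having been screened.

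**The concern.** The number of workshops completed is the dose of treatment received. It is determined after randomisation, and the design fixes it at zero for every control when the outcome is measured. Holding it constant while estimating the effect of assignment compares controls with a hypothetical intervention group that attended nothing. That is not the intent-to-treat contrast promised earlier in the same paragraph.

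The Sample size section says the pilot's goal is a preliminary effect size for a larger trial. An arm estimate pulled towards zero, or made several times less precise, would defeat that purpose and could be misread as a lack of effect.

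**Working it through.** **1. The plan's own figure.** 120 alters with 10% attrition give 120 × 0.9 / 2 = 54 per arm. With 3 alters per index woman and ICC 0.01, the design effect is 1 + 2 × 0.01 = 1.02, and 54 / 1.02 = 52.9, the stated 53. Power for 5% versus 24% with 53 per arm (two-sided 0.05 assumed) is 0.802. The sample-size statement reproduces, so the point does not rest on an error there.

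**2. What the arm coefficient becomes at month 6.** Let A be arm and W workshops completed, with W = 0 whenever A = 0. In a linear model Y = b0 + b1·A + b2·W, the arm difference is b1 + b2 × (mean attendance), so b1 = arm difference − b2 × (mean attendance). Suppose benefit is proportional to attendance, with an assumed mean of 5.6 of 7. Then b2 = 19 / 5.6 = 3.39 points per workshop, and b1 = 19 − 3.39 × 5.6 = 0.

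**3. The interaction.** Because W is zero in controls, A × W equals W for everyone. The product term duplicates the main effect, so the two cannot be estimated together.

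**4. Precision when benefit does not depend on attendance.** Let m and v be the mean and variance of intervention-arm attendance. With 1:1 allocation and equal residual variances, the variance inflation for arm is 1 + m²/(2v). Using the planned binomial variances (0.05 × 0.95 = 0.0475 and 0.24 × 0.76 = 0.1824) and ignoring the small ICC, the variance of the arm estimate is (0.0475 + 0.1824)/54 without W, an SD of 6.5 points. With W it is [0.0475 + 0.1824 × (1 + m²/v)]/54. The article gives no attendance figures, so three assumed distributions are shown.

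| Assumed attendance | m | v | Inflation 1 + m²/(2v) | SD of arm estimate | Approximate power at 19 points |
|---|---|---|---|---|---|
| W not in model | – | – | 1 | 6.5 points | 83% |
| Binomial(7, 0.8) | 5.6 | 1.12 | 15 | 31.4 points | 9% |
| Binomial(7, 0.5) | 3.5 | 1.75 | 4.5 | 16.7 points | 21% |
| Mean 5, SD 2.5 | 5 | 6.25 | 3 | 13.3 points | 30% |

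Power is the normal approximation, from 19/SD against 1.96.

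**5. Simulation at the planned size** (20 index women per arm, 3 alters each, 10% attrition, 5% versus 24%).

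- *Linear model, month 6, Binomial(7, 0.8), benefit through attendance.* The mean arm estimate falls from 19.0 points to within 1 point of zero (−0.5 to 0.9 across runs). Its SD rises from about 6.6 to 32–34 points. Rejection falls from 83–86% to 9–12%. The true coefficient is now zero, so this is false rejection, slightly above 5% with cluster-robust errors on 40 clusters.
- *Linear model, benefit independent of attendance.* The estimate stays at 19 points, and rejection falls to 14–15%.
- *Logistic model, month 6, mean attendance about 5.8 of 7.* With benefit through attendance, the arm log odds ratio falls from 1.84 to 0.07 and power from about 83% to 3%. With benefit independent of attendance, the log odds ratio stays near 1.8, its standard error rises from 0.69 to 1.81, and power falls from 79% to 22%.

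**6. The repeated-measures model (linear version, all alters unscreened at baseline).**

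- W as a time-invariant main effect: time-by-arm stays at 19.0 points (SD 6.6), with rejection unchanged. A term that shifts both time points equally cannot absorb change.
- W as time-varying (0 at baseline, the count at month 6) or interacted with time: the result is that of the month-6 model, an estimate near zero with an SD of about 32 points.

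If the planned interaction is taken with the effect term itself, it is time-by-arm-by-workshops. That equals time-by-workshops, because controls have none, so it falls in the second case.

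**The case against.** The strongest reply is that the plan does not lose its intent-to-treat estimate. It plans a comparison of arms at month 6 with no covariates mentioned, and it describes the mixed model by arm and time-by-arm terms only. The sentence on process variables comes later and may describe a supplementary dose analysis. In the repeated-measures model, a time-invariant workshops term does no harm to the linear time-by-arm estimate. The magnitudes also depend on attendance, which nobody yet knows.

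All of this stands as a limit on the point. A reader might infer that adjustment always removes the intent-to-treat effect, or that the plan has no unadjusted comparison. The text supports neither. What remains is that the sentence says control for, does not mark the step as exploratory, and does not say how attendance enters. Nothing ranks the plain comparison above the adjusted model.

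Two further inferences are tempting and should not be drawn.

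- *That alter knowledge of the index woman's cancer risk is an equally bad covariate because enrolled alters already know of her screening.* Knowing that she was screened is not knowing her risk, and the value used may be a baseline one.
- *That the plan omits treatment history, one of the two stratification factors.* Covariates are listed only as examples, with age as the example for index women. A condensed article need not list them all.

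**Conclusion.** The point holds in a bounded form. As written, the plan allows a post-randomisation measure of treatment received into the analysis of intervention effects, contrary to its stated intent-to-treat approach. In a month-6 arm model, or when attendance is time-varying or interacted with time, the arm effect is a contrast at zero workshops, whatever the attendance distribution.

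The size depends on two unknowns. If benefit runs through attendance, which is the intervention's premise, 19 points becomes roughly zero. If it does not, the estimate stays centred and variance inflates about 3- to 15-fold over the assumed attendance patterns. The repeated-measures figures are from a linear version; the logistic figures are for month 6 only. The arm-by-workshops interaction is not estimable beside the main effect under any assumption.

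The rule should be changed before analysis, because it can give a wrong answer on the primary outcome and costs little to correct.

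**What to change.** - State that workshops completed and other process variables are excluded from every model that estimates the arm or time-by-arm effect.
- Restrict adjustment in those models to pre-randomisation variables, preferably the two stratification factors (age under or over 35, and history of CC-related treatment).
- Report attendance separately, either as an exploratory, non-randomised association within the intervention arm or as a complier-type estimate with arm as the instrument. Drop the arm-by-workshops interaction.

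The cost is wording, with no change to data collection. The stratification factors use a few degrees of freedom when events are few: about 54 × 0.05 + 54 × 0.24 = 2.7 + 13.0, or roughly 16 under the planning assumptions. Penalised estimation would handle this.

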#### Sample size

The small sample limits statistical power, but our goal is to assess the preliminary effect size and other parameters to inform a future larger trial. Assuming 120 alters enroll, attrition rate of 10% among alters (we have retained 90–94% over 12 months in past studies in Uganda) [25, 26], *ICC* = .01 to control for clustering within the alters of each participant, and a 5% rate of receiving CC screening in control alters, the effective sample size will be 53 per arm, enabling us to detect a medium effect size (Cohen’s *d* = 0.57; 19 percentage point difference in CC screening among alters during the 6-month follow-up period), with 80% power (alpha = .05). If ICC is as high as .05, and as few as 80 alters enroll, the detectable effect size = 0.72 (25.5 percentage point difference between groups).

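### Adjusting the arm effect for workshops completed, which is zero for every control woman, contradicts intent-to-treat; several arm interactions in one model would often be inestimable on about 16 events

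*Protocol article*

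**What the plan says.** The Statistical analysis section adopts intent-to-treat for alter screening. It plans a comparison of the arms at each time point and a logistic mixed model with arm and arm-by-time terms. It then adds: "We will control for and examine interaction effects with intervention process variables", with number of workshops completed as the example, and also "characteristics of the index participant (e.g., age), as well as the alter (e.g., position in the network", with knowledge of the index woman's risk as a further alter example. These lists are examples and no upper limit is given. Table 1 names further covariates or potential moderators: five demographic items and social support, each for index and alter, and enacted stigma for the alter.

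Study design says that the control arm receives the intervention only after the month-6 assessments, and that allocation is stratified by age (under or over 35) and history of CC-related treatment.

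The Sample size section assumes "a 5% rate of receiving CC screening in control alters" and a detectable "19 percentage point difference in CC screening among alters during the 6-month follow-up period". It gives the aim as a preliminary effect size, and other parameters, for a larger trial.

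**The concern.** There are two problems, and the first does not depend on sample size.

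**Workshops completed.** This variable is measured after randomisation and is fixed at zero in one arm. Holding it constant while comparing arms removes the part of the effect that works through attendance. What is left is a contrast at zero workshops, where intervention women may be few or absent. That is not the effect of being assigned to the intervention. Its interaction with arm duplicates a column already in the model.

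**Few events.** An interaction with arm needs screening events at different covariate values within each arm. With two or three control events expected, several such terms in one model can easily produce separation, and then there is no finite estimate.

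The effect size carried forward to the larger trial is at stake.

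**Working it through.** **Reproducing the plan's figure.** "Assuming 120 alters enroll, attrition rate of 10% among alters" gives 120 × 0.9 / 2 = 54 per arm. With three alters per index woman and ICC 0.01, the design effect is 1 + (3 − 1) × 0.01 = 1.02, and 54 / 1.02 = 52.9. This matches "the effective sample size will be 53 per arm". For 5% v 24%, a two-sided 0.05 test of two proportions (pooled variance; sidedness is assumed) has power 0.802 at 53 per arm. The arcsine effect size is 0.573, against the stated 0.57. The inputs are therefore read as the authors meant them.

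**Expected events.**
- Design effect real, 120 alters: 54 × 0.05 = 2.7 control and 54 × 0.24 = 13.0 intervention; total 15.7.
- 80 alters, 5% v 30.5%: 36 × 0.05 = 1.8 and 36 × 0.305 = 11.0; total 12.8.
- No effect, 120 alters: 108 × 0.05 = 5.4.

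Sixteen is thus the favourable case. The repeated-measures layout adds no events, because alters must report never having been screened at entry.

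The true odds ratio at the design effect is (0.24/0.76) / (0.05/0.95) = 6.0. The chance of no control event at all is 0.95^54 = 6.3%, so about 6% of trials give no finite odds ratio even unadjusted.

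**Workshops completed, algebra.** Let A be arm (0 or 1) and W workshops completed. W = 0 whenever A = 0, so A × W = W for every woman. The interaction column equals the main-effect column and the model is rank deficient, as it was in 100% of simulated trials. With W as a main effect only, the coefficient of A is the log odds ratio at W = 0.

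**Workshops completed, simulation.** 54 independent alters per arm, 5% v 24%, power counted over all runs:

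| Model | 10–90% range of odds ratio | Power |
|---|---|---|
| Arm only | 2.8–16.6 | 74% |
| Arm + workshops | 0.2–108 | 13% |

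The article gives no attendance rate. Mean attendance of 85% of the seven workshops reproduces these figures closely. A separate run with clustered alters (ICC 0.01), that attendance and three further covariates gave 2.6–17.7 without workshops and 0.17–148 with them.

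**Index and alter covariates, simulation.** Same rates, independent alters, covariates unrelated to outcome. A run has no usable estimate if any coefficient exceeds 8 in absolute value or the arm standard error exceeds 8.

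| Model | Median odds ratio (true 6.0) | No usable estimate |
|---|---|---|
| Arm only | about 6.0 | 6% |
| 3 main effects | 6.2–6.4 | 6–7% |
| 8 main effects | 7.3–7.5 | 6% |
| 5 covariates, 3 arm interactions, normal | 9.2–9.4 | 16–17% |
| 8 covariates, 5 arm interactions, normal | 11.1 | 30% |
| 5 covariates, 3 arm interactions, balanced binary | 4.5–4.7 | 66% |
| 8 covariates, 5 arm interactions, balanced binary | about 4.7 | 76% |

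Ranges reflect separate runs. With clustered alters (ICC 0.01) and another assumed covariate set, interacting three covariates with arm left no estimate in 45% of trials, six in 77% and thirteen in 95%.

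**The case against.** The strongest reply is that the article does not say that all these variables enter one model. The model it sets out first has arm, time and their interaction. Examining interactions is common wording for moderator checks, and Table 1 labels the variables covariates or potential moderators. A condensed article may leave the list and the estimator to the analysis plan. It also plans direct arm comparisons at each time point, so one effect estimate does not pass through the covariate model, and it admits that the small sample limits power. All of this stands. It makes the few-events point conditional on several interactions being fitted together.

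It does not answer the workshops point. There the article states a rule and names the variable, and an analysis plan that followed it would inherit the fault. The article's own caution that the sample may be too small covers mediation, not these models.

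A reader might go further and infer that the planned model inflates the odds ratio, so that the larger trial would rest on too optimistic an effect. The documents do not support that. Among usable fits the median was above 6.0 with normal covariates and below it with balanced binary ones, and the article fixes neither the covariates nor their number. A reader might also infer that covariate control is harmful in itself. With three main effects the inflation is about 5% (6.3 / 6.0), and failure and power hardly change. With eight it is about 25% (7.5 / 6.0).

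**Conclusion.** The point holds in two parts.

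1. Controlling the arm effect for workshops completed conflicts with the stated intent-to-treat approach, and the workshops-by-arm term cannot be estimated. Both follow from the design alone. The size of the precision loss (power 13% against 74%) rests on assumed attendance and would be smaller if attendance varied more.
2. On about 16 expected events, 2.7 of them in controls, three or more index or alter covariates each interacted with arm in one model would often leave no usable estimate: about 16–76% of trials against 6% unadjusted. This rests on the article's 5% and 19-point assumptions, full enrolment, and assumed covariate distributions. Fewer alters or a smaller effect would mean fewer events. The direction of bias in the remaining trials is not determined.

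The wording should be changed before analysis. The point gives no ground for objecting to a few baseline main effects.

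**What to change.** - Do not adjust the primary arm effect for workshops completed or any other post-randomisation process variable. Examine these within the intervention arm only.
- Base the primary alter-screening estimate on arm plus the two randomisation factors (age under or over 35, prior CC-related treatment), clustered on the index woman. Use a penalised (Firth-type) or other small-sample method, so that zero or very few control events still give an estimate. In simulation two covariates left the median odds ratio at 6.0 and power at 74%.
- Examine other index and alter moderators one at a time, in models labelled exploratory, reporting estimates and intervals only.

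The change is to analysis wording; no data collection or sample size is affected. The cost is that moderator results become descriptive.

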### Participants

Women are eligible to enroll as index participants if they are age 18 years or older, have screened for CC within the past year, have stable health status (i.e., not in end stages of disease), and shared their CC screening experience with at least one alter who is perceived to not have screened for CC in the past 3 years. Alter participants are eligible if they are at least 18 years of age, are recruited by an index participant, and report never being screened for CC.

Index participants will be recruited through the RHHJ database of women who have received CC screening and referral from Buyinja and Banda providers who have screened women for CC. An RHHJ staff member or health center provider will inform eligible women of the study, and those who express interest in participating will be referred to the study coordinator for formal eligibility screening and implementation of consent procedures. Women who provide written informed consent will then be administered the baseline assessment and be randomly assigned to the intervention or control arm. To recruit alters, we will use data collected from the baseline survey assessment of female social network members to randomly select 5 alters who know the participant’s CC screening experience (or as many as there are if < 5) and ask the participant if she is comfortable asking 3 of these alters to participate. The index participant will be asked to call each selected alter at the end of the interview to describe the study in the presence of the coordinator, who will schedule a study visit for alters who express interest in participating. If an alter refuses or cannot be reached, a replacement will be randomly selected from the list of alters who know the index participant’s CC screening experience.

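### The bivariate mediator screen appears to leave out study arm, so a mediator-outcome association can arise with no mediation when the intervention also raises screening

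*Protocol article*

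**What the plan says.** The protocol article, under Statistical analysis, states the aim: "We will explore factors that may mediate the intervention effects on the primary outcomes among variables targeted by the intervention". The candidates it names are "internalized CC stigma, disclosure (percentage of alters disclosed to), and engagement in CC screening advocacy". It concedes that "The sample size may be too small to do mediation analysis" and gives the fallback: "we will examine how potential mediators are associated with the primary outcomes and treatment condition using bivariate statistics". Two pairings are therefore named, mediator with outcome and mediator with arm. The text does not say whether the arms are pooled in the mediator-outcome pairing, and it mentions neither stratification by arm nor adjustment for it.

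Under Study design, "The primary outcome is alter CC screening over the 6-month follow-up period". The design figures under Sample size start from "Assuming 120 alters enroll, attrition rate of 10% among alters", with 5% of control alters screened and a detectable difference of 19 percentage points.

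On disclosure, the Participants section has the study "randomly select 5 alters who know" the index woman's screening experience. Replacements come from the same list.

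**The concern.** A bivariate statistic relates two variables. If mediator and outcome are the two, arm is not in it. The candidates are variables the intervention is built to change, so arm is expected to shift them. If the intervention also changes alter screening, arm drives both, and they will be correlated across the whole sample even when, inside each arm, the mediator says nothing about who screens. The screen then cannot tell a mediator from a by-product of treatment, which is what it is there to explore.

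At stake is which components look active when the larger trial is designed. The distortion appears when the pilot shows an effect on screening, which is when its results are most likely to be carried forward.

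**Working it through.** **Inputs from the article (Sample size).** 120 alters, 10% attrition, ICC 0.01, control screening 5%, difference 19 points (so 24% in the intervention arm), 80% power, alpha 0.05. Analysed alters: 120 × 0.9 / 2 = 54 per arm.

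**The article's own figures reproduce.** With 3 alters per index woman the design effect is 1 + (3 − 1) × 0.01 = 1.02, and 54 / 1.02 = 52.9 (stated 53). Two-sided power for 5% v 24% with 53 per arm is 0.802 (stated 80%). Cohen's h is 0.573 (stated effect size 0.57).

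**Assumption.** The article gives no expected effect on any mediator, so a range is used.

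**Binary mediator, no link with screening inside either arm.** With equal arms, the screening rate among alters with the mediator, ignoring arm, is (m0 × 0.05 + m1 × 0.24) / (m0 + m1), where m0 and m1 are the mediator prevalences in control and intervention. For 30% v 70%:
- mediator present: (0.30 × 0.05 + 0.70 × 0.24) / 1.00 = 0.183
- mediator absent: (0.70 × 0.05 + 0.30 × 0.24) / 1.00 = 0.107
- odds ratio: (0.183 / 0.817) / (0.107 / 0.893) = 1.87, although it is 1 within each arm.

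Rejection rates at alpha 0.05 come from 20,000 simulated trials per setting:

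| Mediator, control v intervention | Odds ratio ignoring arm | Chi-square ignoring arm | Mantel-Haenszel by arm |
|---|---|---|---|
| 40% v 60% | 1.4 | about 8% | about 5% |
| 30% v 70% | 1.9 | 20% | about 5% |
| 20% v 80% | 2.6 | 39% to 40% | about 5% |

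**Continuous mediator.** With no mediating effect, r(mediator, outcome) = r(arm, mediator) × r(arm, outcome). Here r(arm, outcome) = (0.19 / 2) / √(0.145 × 0.855) = 0.27. For a mediator shifted by 1.0 SD, r(arm, mediator) = 0.5 / √1.25 = 0.447, so the induced correlation is 0.27 × 0.447 = 0.121. In 4,000 simulated trials per setting, with the mediator measured on the alter or shared by an index woman's alters:

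| Shift in mediator | Induced correlation | Test ignoring arm |
|---|---|---|
| 0.5 SD | 0.065 | 10% to 12% |
| 1.0 SD | 0.121 | 23% to 25% |
| 2.0 SD | 0.191 | 52% |

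Adjusted for arm, the rate is about 5% throughout.

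**Dependence on the screening effect.** At 5% v 5% screening, the test ignoring arm rejects in 4.2% to 5.6% of trials however far the mediator moves. At 5% v 15% it rejects in 7% to 8% for a 0.5 SD shift and 21% to 23% for 2.0 SD.

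**Limit.** Outcomes were drawn independently within index woman given arm. Outcome clustering would raise the error further for index-level mediators tested without allowing for it.

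**The case against.** Five points can be made for the article.

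**Pooling is inferred.** The text never says the arms are combined, within-arm bivariate statistics are not excluded, and a condensed article may leave this to fuller documents. That stands as a limit on certainty. But the article does name a method and its two pairings, and the ordinary reading leaves arm out. The wording should be settled.

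**The analysis is exploratory.** The article doubts its sample is large enough for mediation analysis and sets no threshold or rule for declaring a mediator. That limits the consequence. It does not make a confounded association informative.

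**The artefact is conditional.** A reader might infer that anything the intervention changes will look linked to screening. The figures do not support that: the intervention must also change screening, and even at 20% v 80% the test ignoring arm is non-significant in about 60% of trials.

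**Adjustment costs power.** At 5% of 54, about 2.7 control alters screen, so nearly all within-arm information comes from the intervention arm. With a true within-arm odds ratio of 3, arm-stratified power is 35% at 30% v 70% and 26% at 20% v 80%, before any clustering loss. This stands. The 75% power of the test ignoring arm at 30% v 70% is not a fair comparator, since much of it is the signal induced by arm.

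**Disclosure is not fixed.** Because enrolled alters already know the index woman's screening experience, a reader might infer that disclosure is complete in both arms and cannot mediate their screening. The article does not support this. Table 1 lists disclosure of screening and treatment results, and the Statistical analysis section treats an alter's knowledge of the index woman's cancer risk as something that varies.

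**Conclusion.** The concern holds in a limited form. If the mediator-outcome association omits arm, as the wording suggests, and the intervention raises both mediator and screening, the association is confounded by arm. At the article's 5% v 24% with 54 alters per arm, the false-positive rate is about 8% to 40% across the assumed binary shifts, against about 5% when stratified. The size rests on mediator shifts the article does not give and on a real effect on screening; without that effect there is no inflation. The consequence is confined to which candidates look promising for a later trial. This is an inexpensive improvement to an exploratory analysis, not a fault in the primary one.

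**What to change.** In the Statistical analysis section, say that each mediator-outcome association will be estimated within arm or adjusted for arm (Mantel-Haenszel, or a model containing arm and mediator), with standard errors clustered on the index woman. Report mediator by arm as a separate description. Present both as descriptive: the mediator is not randomised, so even a within-arm association does not establish mediation.

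For "disclosure (percentage of alters disclosed to", it is enough to note that enrolled alters already know the index woman's screening experience, so the network-wide percentage should be interpreted with that in mind. Do not state that disclosure cannot mediate.

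The cost is wording and one model term, with no new data. Intervals will be wider and power low, and the report should say so, so that a null within-arm result is not taken as evidence against a mediator.
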